**Table 5 Tab5:** **exercise modalities**

Treatment regimens:	Motor control therapy	General active exercise therapy	Isometric training therapy
Total intervention time	70 minutes	70 minutes	70 minutes
Warming up	10 minutes	10 minutes	10 minutes
Cooling down	10 minutes	10 minutes	10 minutes
Regime specific intervention time	50 minutes	50 minutes	50 minutes
Intensity	Low load	60% 1RM	30-40% MIS
Number of sets	2	3	2
Number of repetitions	20	20	20
Duration of one repetition	6 seconds	-	5 seconds
Rest between sets	30 seconds	30 seconds	30 seconds

*1RM: one repetition maximum, MIS: maximal isometric strength.*

#### General active exercise therapy

General active therapy has proven to be an effective therapeutic approach in nonspecific LBP [5, 6, 14]. These patients receive a global form of exercise therapy existing of all kinds of active exercises. These exercises do not have the direct purpose of contracting the multifidus or transversus abdominis. Aerobic conditioning exercises will be performed for lower and upper limbs, strength training of the back and abdominal muscles and stretching (Tables 4 and 5).

#### Isometric training therapy

Effectiveness of isometric training therapy has been proven in nonspecific LBP [11–13]. The Tergumed™ (version 1.0, Enraf-Nonius NV, Boom, Belgium) training protocol is followed. It contains progressive resistance isometric training of lumbar trunk muscles on devices in the directions flexion, extension, rotation and lateral flexion. In the first session, the maximal isometric strength is determined in all movement directions to set the level of resistance for training. During the first to fourth week, patients train at 30%, and during the fifth till ninth week, at 40% of their maximal isometric strength. When the difference in maximal isometric power for rotation or lateral flexion direction between abdominal and back muscles exceeds 20%, the weaker side has to perform five sets and the stronger side has to perform four sets (Tables 4 and 5). Exercises mentioned in Table 4 are further explained in Additional file 1, which explains the performance of each exercise.

### Power analysis

#### Derivation phase

As we cannot predict the therapeutic effect in the derivation phase, we use a two-tailed hypothesis to calculate the power. A pilot study showed that the standard deviation of our primary outcome measure, the MODI, is comparable to the results of Brennan *et al*. [17]. Given these estimates, 120 patients are needed to detect a minimum clinically important difference (effect size 0.43) with 80% power using a two-tailed hypothesis. This means that three groups of 40 patients are needed to complete the whole trial. Since Van der Wouden *et al*. [34] mentioned a dropout rate of 54%, we aim to include 260 patients.

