**Discussion:**

A randomized controlled trial has not previously been performed for the development of a CPR for exercise therapy in CLBP patients. Only one CPR was described in a single-arm design for motor control therapy in sub-acute non-radicular LBP patients. In this study, a sufficiently large sample will be included in both the derivation and validation phase.

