#### Validation phase

In the validation phase the intervention therapy stays the same, but new patients will be included. In this study design, the interest is that treatment success will be higher in the matched group than the unmatched group, which means a one-tailed hypothesis is used to calculate the power. In the validation phase we need 105 patients to detect a minimum clinically important difference (effect size 0.43) with 80% power using a one-tailed hypothesis. This means that three groups of 35 patients are needed to complete the whole trial. Again we assume a dropout rate of 54% into account and therefore aim to include 229 patients.

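### The stated sample sizes of 120 and 105 do not follow from effect size 0.43 and 80% power, do not agree with each other, and in the derivation phase match no planned analysis

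*Protocol article*

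**What the plan says.** All references are to the protocol article.

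- **Power analysis, Derivation phase:** "120 patients are needed to detect a minimum clinically important difference (effect size 0.43) with 80% power using a two-tailed hypothesis". This is presented as three groups of 40. The section refers to the standard deviation (SD) of the Modified Oswestry score (MODI) from a pilot and an earlier trial, but gives no value.
- **Power analysis, Validation phase:** "we need 105 patients to detect a minimum clinically important difference (effect size 0.43) with 80% power using a one-tailed hypothesis". This is presented as three groups of 35, and the comparison is matched against unmatched treatment.
- **Randomization and blinding:** matched and unmatched patients are held at 50:50 within each intervention group in the validation phase.
- **Data analysis, Derivation phase:** success is a fall of at least six MODI points. Predictors are screened and entered in a regression separately for each treatment group.
- **Data analysis, Validation phase:** a three-way repeated-measures analysis of variance over four time points.
- **Abstract, Discussion:** "a sufficiently large sample will be included in both the derivation and validation phase". The main Discussion repeats this and rests it on the power analysis.

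The power sections do not state alpha, the test, the type of effect size or a correlation. For the derivation phase they name no comparison.

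**The concern.** The article states the number of patients, the effect size, the power and the number of tails, so the four can be checked against each other. The two phases share the effect size and the power and differ only in tails ("we use a two-tailed hypothesis to calculate the power" against "which means a one-tailed hypothesis is used to calculate the power"), so the totals can also be checked against one another. Both checks fail on the ordinary reading.

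The article relies on this calculation to call its sample adequate, and it notes that an earlier derivation study reported none. If validation shows no difference, readers will take it as a negative result at 80% power. The recruitment targets of 260, 229 and 489 are built on 120 and 105. In the derivation phase the power statement gives no assurance about the task actually planned, which is choosing predictors within an arm.

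**Working it through.** **Inputs from the article.** Effect size 0.43; power 80%; two-tailed with N = 120 (3 × 40); one-tailed with N = 105 (3 × 35); matched:unmatched 50:50; dropout 54%.

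**Assumptions.** Alpha = 0.05; the nearest anchor is the P < 0.05 used at the regression stage. 0.43 is a standardised mean difference d, because it is called a clinically important difference and is tied to an SD. If the six-point success threshold is the difference meant, which the article does not say, the SD would be 6/0.43 = 14.

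**1. Dropout step.** 120/0.46 = 260.9 and 105/0.46 = 228.3, against 260 and 229; 260 + 229 = 489. This step is sound, so the question is only about 120 and 105.

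**2. Patients needed, two equal groups.** n per group = 2(z_alpha + z_power)²/d².
- Two-tailed: 2 × (1.960 + 0.842)²/0.43² = 84.9. The t-test gives 85.9, so 86 per group and **172** in total, not 120.
- One-tailed: 2 × (1.645 + 0.842)²/0.43² = 66.9. The t-test gives 67.6, so 68 per group and **136** in total, not 105.

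**3. Power of the stated numbers.** Power ≈ Φ(d√(n/2) − z_alpha), with n per group.

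| Comparison | d√(n/2) − z_alpha | Normal | t-test | d detectable at 80% (t-test) |
|---|---|---|---|---|
| 105, matched v unmatched (52.5 each on average), one-tailed | 2.203 − 1.645 | 71.2% | 70.7% | 0.49 |
| 120 as 60 v 60, two-tailed | 2.355 − 1.960 | 65.4% | 64.7% | 0.52 |
| Two arms, 40 v 40, two-tailed | 1.923 − 1.960 | 48.5% | 47.6% | 0.63 |

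The first row uses a comparison, split and tail that the article gives. The second is a best case for 120; the article has three arms and describes no 60 v 60 split.

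**4. The totals against each other.** For one common two-group comparison at alpha 0.05, moving from two tails to one multiplies N by (1.645 + 0.842)²/(1.960 + 0.842)² = 0.79. So 120 would become about 95. The article has 105/120 = 0.875.

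**5. Other readings.**
- *Alpha 0.10:* 76% for 120 two-tailed and 82% for 105 one-tailed. Exactly 80% would need alpha of about 0.13 and 0.087 respectively.
- *0.43 as the ANOVA effect size f:* about 56 in total for three groups, or 70 for a four-degree-of-freedom interaction.
- *f = 0.43/2 = 0.215, three groups:* 212.
- *One-sample or paired test in each arm:* 35 one-sided, and 3 × 35 = 105; but 45 two-sided, and 3 × 45 = 135, not 120.
- *Baseline adjustment, variance factor 1 − r²:* 120/171.7 = 0.699 gives r = 0.55; 105/135.1 = 0.777 gives r = 0.47. No one value serves both.

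**6. Match to the analysis.** The derivation analysis contains no comparison of mean MODI between groups. It relates baseline variables to success within one arm of about 40, so the 80% figure has no planned test to refer to.

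**The case against.** The strongest reply is that 65% and 71% are not established as the power of this design. Alpha, the d reading and a single-time-point t-test are all supplied from outside, and the planned validation analysis uses repeated measures. Suppose d = 0.43 applies to the mean of the three follow-ups with common correlation r, so that the variance is multiplied by (1 + 2r)/3. Power for 120 two-tailed and 105 one-tailed is then 82% and 85% at r = 0.5, and 74% and 79% at r = 0.7.

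This stands as a limit on the wording. A reader might infer that the trial is shown to have only 71% power, and the documents do not support that. But the reply does not restore the stated figures. No correlation is given, and exactly 80% would need r of about 0.55 for 120 and 0.67 for 105. The averaged comparison is also not the three-way interaction that the article tests. Two repeated-measures interaction settings do come within four patients of both totals (122 and 101). They require halving 0.43 to f = 0.215, assuming a correlation of 0 or 0.3, and letting alpha 0.10 stand in for one tail. None of this is stated.

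Three other stronger readings also fail:
- *That no standard reading gives either number.* A one-sided one-sample test per arm gives 105 exactly. It is not the matched versus unmatched comparison, and its two-sided form does not give 120.
- *That every per-arm comparison has less power.* This is true of arm against arm, but a within-patient change in one arm has about 76% (40, two-sided) and 80% (35, one-sided).
- *That matched patients might be only a third of the validation sample.* The article fixes 50:50.

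It is also fair that a journal article may leave the test and alpha to a fuller document. The point here is not the omission: the figures that are printed do not fit together. Better retention than assumed would raise power, but the article presents 120 and 105 as the numbers that give 80%.

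**Conclusion.** Wrong as written. With d = 0.43 and alpha 0.05, a two-group comparison needs about 172 and 136 patients rather than 120 and 105. The firmer result is for validation: 105 completers split 50:50 give about 71% power, one-tailed, unadjusted and at a single time point, or 80% for an effect of 0.49. For derivation, 120 gives at best about 65%, and about 48% between two arms of 40; the larger fault there is that the claim describes no planned analysis.

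The disagreement between the two totals (0.875 against 0.79) does not depend on the value of d or on how the patients are split, though it does assume one common two-group comparison at alpha 0.05. None of the standard readings tried reproduces both totals. The percentages hold only under the stated assumptions and are not a measurement of the power of the repeated-measures analysis.

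**What to change.** Leave recruitment unchanged and correct the text.

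- **Power analysis, Validation phase:** say that 105 completers give about 71% power for 0.43, or 80% for 0.49, in a one-tailed, unadjusted comparison of matched and unmatched patients at one time point. If baseline adjustment or repeated measures are meant to restore 80%, state the alpha, the test and the assumed correlation, and recompute both totals on that one basis.
- **Power analysis, Derivation phase:** delete the 80% claim and say that 120 is not sized on a between-group test.
- **Both power sections:** define the effect size and give the SD and the difference behind 0.43.
- **Abstract and main Discussion:** qualify the statements that the sample is sufficiently large.

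The cost is wording and a less favourable power statement. No extra patients are needed.

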### Data analysis

#### Derivation phase

This phase aims to detect potential predictive variables for treatment success (dichotomous, yes or no) in a set of baseline measurements. A minimal decrease in the MODI score of six points is considered as treatment success [35].

Potential predictive variables are selected as follows: first, individual variables from the self-reports, history and physical examination are tested for their bivariate association with the reference standard using independent sample t tests, Mann-Whitney U tests or chi-square tests based on the nature of the data. Variables with a significance level of *P* <0.10 are retained as potential prediction variables. We chose a more liberal significance level at this stage to avoid excluding potential predictive variables.

Next, selected potential prediction variables and known predictors as determined in the study of Hicks *et al*. [16] are entered into a multiple linear regression equation to determine the optimal set of predictors. A significance of *P <*0.05 is used in this stage. Variables retained in the regression model are used to develop a multiple CPR for classifying patients as likely responders to treatment. This statistical analysis is performed for each treatment group (motor control therapy, general active exercise therapy and isometric training therapy).

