#### Validation phase

In the validation phase new patients will be again assigned randomly into one of the three treatment groups. Based on the derived CPR determined in phase one, each intervention group will be divided into either ‘matched therapy’ or ‘unmatched therapy’. The recruitment, information form, informed consent, measurements, blinding and intervention procedure will be the same for both derivation and validation phase.

To verify intergroup differences at baseline, variables will be compared between groups using independent t tests, Mann-Whitney U tests, or chi-square tests of independence based on the nature of the data.

To examine the principle hypothesis (difference in treatment effect between matched and unmatched groups), a three-way repeated-measures analysis of variance will be performed with treatment group (motor control versus general active exercise therapy vs. isometric therapy) and classification subgroup (motor control versus general active exercise therapy versus isometric therapy) as between-subject variables and time (baseline, nine weeks, six months and one year) as the within-subject variable. The dependent variable is disability (MODI score). The hypothesis of interest is the three-way interaction, and the two-way interactions between time and treatment group and between time and classification subgroup. We hypothesize that outcome over time will not differ based on the randomized treatment group, or the classification subgroup, but will depend on the interaction between the treatment group and classification subgroup, such that patients randomized to matched treatment will have better outcomes than patients randomized to unmatched treatment. This hypothesis will be supported if the three-way interaction is significant, but the two-way interactions are not. Pairwise *post-hoc* comparisons will be performed at each follow-up period to further explore any significant interaction terms. In both the derivation and validation phase we will use an intention-to-treat analysis.

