Third, we aim to include a sufficiently large sample, based on a power analysis. Hicks *et al*. [16] included 54 patients in their study but no power analysis is mentioned in their paper. If there are not enough patients included, the CPR is unlikely to be valid. We compared our calculated sample size with the sample size calculated in Brennan *et al*.’s [17] study design and found comparable results. In addition, we use an extra 54% inclusion target to compensate for the possible dropout rate [34]. We aim to recruit 489 patients in total (combined total for both phases of the study). We calculated that each year around 200 LBP patients start the back revalidation program in the Antwerp University Hospital. This is the same for the Apra Rehabilitation Hospital. Out of these 400 LBP patients around 50% have nonspecific complaints. This means that we need around 18 months to finish each phase. We will closely follow the inclusion procedure to make sure we meet our goals. The current study protocol describes only the derivation and validation phase, and not the impact phase. Future research should target this impact phase. The impact phase needs a completely different approach since it investigates the economic consequences of the implication of the CPR. It also depends on the outcome of the derivation and validation phase. Consequently, it is beyond the scope of the present paper.

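### The derivation power statement is about a MODI difference that the derivation analysis never tests, so it cannot support the claim that the sample behind each prediction rule is large enough

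*Protocol article*

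**What the plan says.** **Power analysis, Derivation phase.** The calculation rests on the standard deviation of the MODI, which a pilot study found comparable to that of a cited trial. It concludes that "120 patients are needed to detect a minimum clinically important difference (effect size 0.43) with 80% power using a two-tailed hypothesis". This becomes three groups of 40, and enrolment is raised to 260 for an assumed dropout of 54%. The comparison, the alpha and the numerical SD are not given.

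**Data analysis, Derivation phase.** The aim is to find baseline predictors of treatment success, a yes/no outcome defined by a fall of at least six MODI points. Each candidate is screened against success at P<0.10. The survivors, with the known predictors from the earlier rule study, then enter a regression at P<0.05. "This statistical analysis is performed for each treatment group", and the Abstract confirms that one rule is derived for each therapy.

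**Claims of adequacy.** The Abstract states: "In this study, a sufficiently large sample will be included in both the derivation and validation phase". The main Discussion makes the same claim and rests it on the power analysis. It notes that the earlier rule study had 54 patients and reported no power analysis, and warns: "If there are not enough patients included, the CPR is unlikely to be valid".

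**The concern.** A sample-size calculation supports a design only for the test it was made for. This one concerns a mean difference on the outcome scale. The analysis it is meant to support compares patients who succeed with patients who do not, on baseline variables, inside one therapy, three times over. The two share neither the variable nor the groups nor the number of patients.

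The article nonetheless uses the calculation as evidence that the derivation sample is adequate, and presents this as an advance on a study it criticises for lacking such a calculation. A reader would conclude that each rule comes from a sample shown to be large enough to find its predictors. Nothing in the article shows that. The later validation phase tests the rules that were derived, but it cannot recover a predictor missed at derivation.

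**Working it through.** **1. The plan's own figures.** Inputs from the Power analysis: effect size 0.43, 80% power, two-tailed. Alpha is not stated; 0.05 is assumed.

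- Two-group comparison of means: n per group = 2 × ((1.960 + 0.842)/0.43)² = 84.9, so 85 per group, which is 170 for two groups or 255 for three.
- The stated 120 is not reproduced. A paired or one-sample test needs 45, and a three-group F test needs 56 (f = 0.43) or 212 (f = 0.215). An unstated variance reduction cannot be excluded, because the SD and method are not given. The point here does not depend on this: a correct 120 would still be for a MODI difference.
- Dropout: 120/(1 − 0.54) = 260.9, against 260 stated, which agrees apart from rounding.

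**2. Patients behind each rule.**

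- Enrolled: 260/3 = 86.7, about 87 per therapy.
- Expected completers: 260 × 0.46 = 119.6, so about 40 per therapy.
- Earlier single-arm study (Background): 54 patients, all of whom informed the motor control rules. 40/54 = 0.74, or 26% fewer.

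**3. What was sized against what is analysed.**

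| | Power analysis | Derivation analysis |
|---|---|---|
| Variable compared | MODI | Each baseline candidate |
| Groups compared | Not named | Success versus no success |
| Patients per analysis | 120 in three groups of 40 | One therapy only |
| Threshold | Two-tailed, alpha not stated | P<0.10 screen, then P<0.05 in the regression |

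A between-therapy reading and a before/after reading of the left column both fail to match the right column.

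**4. What each rule's sample can detect.** The success rate is not given, so two splits are assumed: 50:50, and 72:28 (39 of 54 improved in the earlier study, 39/54 = 72%). For a continuous predictor and a two-sample t test, the detectable difference in SD units is approximately (z for alpha + 0.842) × √(1/n₁ + 1/n₂). The table gives the slightly larger exact noncentral-t values at 80% power.

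| Patients in one therapy | Split | P<0.10 screen | P<0.05, simple two-group test |
|---|---|---|---|
| 40 | 20/20 | 0.80 SD | 0.91 SD |
| 40 | 29/11 | 0.90 SD | 1.02 SD |
| 87 | 43.5/43.5 | 0.54 SD | 0.61 SD |
| 87 | 63/24 | 0.60 SD | 0.68 SD |

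Example for the first cell: (1.645 + 0.842) × √(1/20 + 1/20) = 0.79 by the approximation, 0.80 exactly.

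The P<0.10 column is the one the plan's bivariate tests use. The last column is only a guide, since the plan applies P<0.05 within a multivariable regression.

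**5. Precision of a likelihood ratio.** The earlier study reported a positive likelihood ratio of 4.0 (95% CI 1.6 to 10.0) with 54 patients. SE of its logarithm = ln(10/1.6)/3.92 = 0.467. If the SE scales with 1/√n:

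- 40 patients: 0.467 × √(54/40) = 0.543, CI about 1.4 to 11.6.
- 87 patients: 0.467 × √(54/87) = 0.368, CI about 1.9 to 8.2.

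So precision would be worse than the earlier study's with 40 patients and better with 87.

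**The case against.** The best counter-argument is that 40 is the low end. About 87 per therapy are enrolled and intention-to-treat is specified for derivation. The 40 are those who complete the whole trial, which runs to one year, and the article does not say at which visit success is judged. If it is nine weeks, more than 40 may have outcomes. This stands: the comparison with 54 is conditional, and the detectable difference must be given as a range. It does not repair the mismatch, because the power statement does not address 87 patients per rule any more than 40.

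Several stronger readings are tempting but are not supported:

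- **That the 120 was calculated to compare therapies.** This is a natural guess from three groups, but the Power analysis names no comparison.
- **That the plan expects the therapies not to differ.** "We hypothesize that outcome over time will not differ based on the randomized treatment group, or the classification subgroup" belongs to the validation phase. For derivation, the Power analysis says that the effect cannot be predicted.
- **That power for a predictor is 22% to 26%.** That applies 0.43, a MODI effect size, to a baseline predictor, and uses P<0.05 where the bivariate screen uses P<0.10. The known predictors from the earlier study enter the regression whatever the screen shows.
- **That the rules are presented as final.** They are to be tested in new patients, so they are already provisional by design. Nor does the article plan to read a missed predictor as evidence of absence.
- **That the Discussion sets 54 as a minimum.** It criticises the absence of a power analysis and adds a general warning about small samples.

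**Conclusion.** The concern holds in a limited form. The article justifies the derivation sample with a calculation for a MODI difference, while the derivation analysis tests no such difference. The adequacy claimed in the Abstract and Discussion is therefore unsupported for the derivation phase. This does not show that the sample is too small for every useful predictor; that depends on predictor strength, the success rate and retention, none of which the article fixes.

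In size: with the plan's assumed dropout, each rule has about 40 completers and can detect predictor differences of 0.80 to 0.90 SD at the screen with 80% power. With all enrolled patients contributing, the figure is 0.54 to 0.60 SD. These values assume a continuous predictor, a t test and success splits of 50:50 or 72:28. The correction should be made, but it does not prevent the trial from proceeding.

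**What to change.** 1. **Power analysis, Derivation phase:** name the comparison behind the 120, and state that it does not size the selection of predictors within each therapy.
2. **Same section:** add the detectable difference per rule at the P<0.10 screen, from 40 patients (expected completers, 0.80 to 0.90 SD) to 87 (all enrolled, 0.54 to 0.60 SD), with the assumed success splits.
3. **Abstract and main Discussion:** remove or qualify the claim of an adequate sample for the derivation phase.
4. **Main Discussion:** qualify the contrast with the 54-patient study by saying that each rule here is expected to rest on about 40 completers, and on more only if retention is better than assumed or missing outcomes are handled so that those patients contribute.

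Adding a comparison of MODI between therapies to justify the 120 afterwards is not advised. At an effect size of 0.43, 40 against 40 gives about 48% power (two-sided 0.05), so it would be an underpowered test that still says nothing about the rules.

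The cost is wording and a less favourable stated claim. No extra patients, visits or data are needed.
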